**C. Subject Selection**

i. Main Study

**1. Who and Why**: The target population for the study is out-of-school adolescent female orphans living in urban -Zimbabwe. Females aged 16 to 19 years will be recruited. We restricted the intervention to females because prevalence data clearly show that girls are at higher risk for HIV infection. We hypothesize that an economic livelihood intervention will have greater effect on our biological and behavioral outcomes in females, as it will create alternatives to transactional sex, which is overwhelmingly practiced by females for accessing resources and gaining status. Sixteen is the legal age of consent in Zimbabwe, thus, we are able to collect and test biological specimens and provide results without obtaining parental or /guardian consent. We have chosen our upper age range as 19 because this is consistent with literature on the definition of adolescents [69]. We have restricted our sample to those girls not currently in school, and who have not already graduated from secondary school. The vulnerability of out of school girls (reflected through current HIV trends) also indicates a lack of access to: knowledge of health risks, skills in communication and negotiation, and to condoms and youth friendly services, which provide needed services at a convenient time and place, in a manner that satisfies adolescents’ concern over confidentiality [70, 71].

**2. Numbers**: One hundred fifty individuals will be randomly assigned to the treatment arm and 150 to the control arm, for a total of 300 participants.

**3. Inclusion/Exclusion Criteria:**

i. In order to be eligible for the study, a participant must be female; an orphan (defined as having lost at least one parent); aged 16-19; out-of-school; willing to undergo HSV-2, HIV and pregnancy testing; HSV-2 and HIV negative; not pregnant; able and willing to sign an informed consent form to join the study; willing to be randomized and, if selected for the control group, to defer receipt of the economic livelihood aspect of the intervention until after the study is complete (assuming the intervention is successful); and able to speak Shona or English.

ii. Prevention for Positives cohort: An additional cohort of 50 participants will be recruited from the same population as the main study to test the feasibility of a expanding the study to HSV-2 and HIV positive participants and explore the process of integration and enhancements necessary for future scale up. We hypothesize that the inclusion of positives into this study will, with minor adjustments, be more effective in empowering positive adolescents with improved livelihoods, better access to care and treatment and slower disease progression (compared to LifeSkills alone). Additionally, we hypothesize that positive girls will not experience additional marginalization and stigma within the study or community as a result of their disease status. The only difference in inclusion/exclusion criteria for the additional 50 girls is that those who test positive for HSV-2 or HIV will not be excluded from the study

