**Economic Opportunity for Zimbabwean Adolescent Orphans**

1. **Study Aims**

The overall aim of this project is to determine, using a randomized controlled design, whether a economic livelihood (in this case vocational training package including monthly fees, a modest stipend based on progression and performance in the training program, and a completion bonus) and life-skills intervention, designed to increase control over sexual interactions, prevents the adverse consequences of unprotected sex among out-of-school female orphans aged 16-19 in Zimbabwe compared with a life-skills intervention alone.

**Aim 1: To assess the effectiveness of a combined vocational training package and life-skills education intervention in reducing the incidence of our primary outcomes: Herpes simplex virustype 2 (HSV2) and unintended pregnancy.** Although not powered to assess HIV as an outcome, we will nevertheless monitor HIV incidence between groups. (Note that rates of bacterial STDs are too low to consider.) We hypothesize that compared to those in the control group, adolescent female orphans receiving the combined intervention will experience a lower incidence of these outcomes.

Aim 2: To assess the effectiveness of a combined vocational training package and life-skills education intervention in reducing our secondary outcomes: high-risk behaviors (e.g., unprotected sex, number of partners, transactional sex, early sexual debut, sexual coercion and violence). Our hypothesis is identical to that for Aim 1.

**Aim 3. To examine the intermediary effects of increased economic opportunity, social support, and improved sexual negotiation skills in enhancing participants’ control over sexual interactions.** We hypothesize that the combined intervention will enable participants to, for example, increase and gain control over their income and future income-earning potential (through the vocational training intervention), thereby empowering them to use the sexual negotiating skills gained through the life-skills intervention. Together, these outcomes will increase participants’ control over sexual activity, and reduce the prevalence of sexual risk behaviors and the incidence of both HSV-2 and unintended pregnancies. This aim will allow us to examine why the intervention is or is not effective. Furthermore, if the predictive value of these outcomes is high, this may obviate the need for collection of biological data and self-reports of sensitive behaviors in future studies.

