**E. Consent Process and Documentation**

All potential study participants will have the opportunity to meet with study staff one-on-one to learn about the study and ask questions for clarification. The participants will be told that they are being asked to participate in a confidential study about improving economic opportunities and reproductive health among adolescent female orphans. They will be told that participation involves periodic interviews and biological sample collection for HIV, HSV-2 and pregnancy testing, whether or not the participant is sexually active. Randomization will also be explained and participants will be told that if they participate, and if they are selected for the control group, they will receive the economic component of the intervention after the study is complete, assuming we observe an efficacious result. They will be told that some of the questions examine high-risk sexual behaviors, as well as other sensitive issues. They will be told that trained nurse/counselors will collect biological specimens and administer data collection surveys every six months for a period of three years.Participants will be told that they have the right to refuse or withdraw from the study at any time. The research objectives, the tests performed, and the names and telephone numbers of the interviewer and local principal investigator/project director will be told verbally to all participants, and summarized in an “information sheet,” with which they will be provided. If the individual is eligible and agrees to participate, study staff will explain the terms of the study’s consent form. If the prospective participant consents, she will be asked to sign the consent form. The consent form will be available in Shona and English. It may be intimidating for young people to sign a consent form, and they may feel that it will impinge upon confidentiality. Thus, participants who feel uncomfortable signing the consent form will be asked to put a mark (but no signature) at the bottom of the document to denote their consent.

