Once making her selection, the participant will be placed in one of the three training courses that will take place over a 6-month period with the objective to acquire vocational skills and practice life skills. Based on monthly assessments of attendance, training fees will be paid directly to institutions and participants will receive a stipend for transport and basic food requirements. Fees and stipends will be withdrawn if the participant does not attend at least 80% of the sessions. If participant falls ill or is otherwise unable to attend for legitimate reasons, participants will be allowed to make up sessions. The participant is also required to meet with her guidance counselor at least once. At the end of the training session, if the participant attended at least 80% of the sessions, passed the final exam and made guidance counselor contact she will be eligible for a bonus (equivalent to US$100), contingent upon working with her guidance counselor to develop a plan to use this bonus towards ongoing education, accessing credit or starting up a business using her acquired skills or to secure employment. The participant will have two chances to pass her final examination. At this stage, the guidance counselor will assist the participant in linking to jobs, accessing further training and micro-credit as appropriate. Throughout the course of the study, staff will have ongoing contact with the participant during SHAZ! reunions with her initial life skills class and study visits at alternating 6 month intervals.

ii. Control Group

The control group will have a comparable experience for all aspects of the intervention, except for the vocational training and accompanying monthly fees, stipend and completion bonus, and the personalized guidance counseling. After the first year of the study, the intervention will no longer be delivered. We will follow-up participants from both arms for one additional year, conducting follow-up ACASI interviews and the same biological tests every six months.

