To ensure high follow-up rates, at the completion of the participants life skills and health training sessions, intervention and control participants will participate in a graduation ceremony, and then will meet together again in SHAZ reunions every six months, identical to the intervention participants. They will not have access to guidance counseling or vocational training, but will be followed-up for the same amount of time at the same intervals as the intervention participants. Every participant will be provided with condoms and hormonal contraception if requested, and screening and treatment for symptomatic STIs. Referrals for health care will be provided on an as needed basis. Life-skills facilitators/mentors will continue to meet with their peer support groups on a monthly basis for the remainder of the study.

At the end of the study, all control participants who completed a final study visit will be offered the same vocational training that was offered to the intervention participants. The study will cover the fees of the vocational training program for 6 months, but will not provide the transport reimbursement or bonus, or the supportive guidance counseling.

**2. Time:** It will take approximately 15 minutes to explain the study and approximately 30 minutes to get informed consent. The screening interview will take 15 minutes, while the baseline and follow-up interviews will be limited to 30-45 minutes. HIV pre-test counseling will take about 30 minutes, and the time for post-test counseling will depend on the participant’s needs. Blood and urine specimen collection will take ten minutes. Pregnancy counseling will take five to ten minutes.

**3. Study Sites:** Study visits will take place in a family health clinic in Chitungwiza, an urban site-outside of Harare, Zimbabwe.

**G. R**isks/Discomforts

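### Controls are told at entry that the deferred economic component depends on trial success, but the procedures offer a smaller package to every control who completes the final visit, whatever the result

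*Protocol*

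**What the plan says.** Three places in the Protocol describe what the control arm receives after the study.

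- **Section C, item 3 (Inclusion/Exclusion Criteria):** a girl must be willing, if assigned to control, "to defer receipt of the economic livelihood aspect of the intervention until after the study is complete (assuming the intervention is successful").
- **Section E (Consent Process and Documentation):** participants will be told that, if they are controls, "they will receive the economic component of the intervention after the study is complete, assuming we observe an efficacious result".
- **Section F, Overview of Intervention, ii (Control Group):** when the study ends, "all control participants who completed a final study visit will be offered the same vocational training that was offered to the intervention participants". The next sentence limits the content: "The study will cover the fees of the vocational training program for 6 months, but will not provide the transport reimbursement or bonus". It leaves out guidance counselling as well.

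The yardstick for content is in section 1 (Study Aims), which describes the economic livelihood intervention as a "vocational training package including monthly fees, a modest stipend based on progression and performance in the training program, and a completion bonus". The Control Group text describes what separates the arms during the study in similar terms: controls have a comparable experience "except for the vocational training and accompanying monthly fees, stipend and completion bonus, and the personalized guidance counseling".

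**The concern.** Accepting the deferral is an inclusion criterion, so each girl agrees to these terms in order to enter. The participants are orphans aged 16 to 19, for whom parental or guardian consent is not required. The terms are also material. The completion bonus is equivalent to US$100 (section K), and the background section says most Zimbabweans earn less than US$550 a year.

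Staff following the consent section and staff following the Control Group section would tell the same control girl different things about whether she will be offered anything, what it depends on and what it contains. The final-visit condition is the one term that gives a control a reason to keep attending, and it is absent from the terms described at entry. That visit supplies the last HSV-2 and pregnancy tests and the second time point of the Aim 2 comparison of initial and final behaviour.

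**Working it through.** There is no figure to reproduce; the check sets the texts side by side.

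**Step 1: condition.** The inclusion criterion and the consent section require a successful or efficacious result and mention no final visit. The Control Group section requires a completed final visit and mentions no result.

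**Step 2: content.** The inclusion criterion and the consent section refer to the economic aspect or component with no stated limit. Against the Study Aims definition:

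| Element | Study Aims definition | Control Group offer |
|---|---|---|
| Training and fees | included | included, six months |
| Stipend | included | not listed; transport reimbursement expressly excluded |
| Completion bonus | included | expressly excluded |

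Guidance counselling is also excluded from the offer, but the Study Aims definition does not name it. The shortfall therefore rests on the bonus and the transport support. In the intervention arm, the stipend is what pays for transport and basic food.

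**Step 3: combine the two conditions.** With two trial results and two visit outcomes there are 2 × 2 = 4 situations for a control:

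| Trial result | Final visit | Inclusion criterion and consent section | Control Group section |
|---|---|---|---|
| Successful | Completed | Economic component, no limit stated | Training with fees only |
| Successful | Missed | Economic component, no limit stated | No offer (by implication) |
| Not successful | Completed | Nothing promised | Training with fees only |
| Not successful | Missed | Nothing promised | No offer (by implication) |

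The texts agree only in the last row. In the first two rows the control gets less than she was told; in the third she gets more.

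**Step 4: look for a reconciling text.** None was found. The Study Aims, the General Study Design, the Intervention Group description and section K do not say which statement governs.

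**Step 5: who is still affected.** Section 4.A reports main-study enrolment complete at 315. It also plans 50 further participants, randomised in the same way under criteria that differ only in HIV and HSV-2 status. Their controls would enter under the contradictory wording, and current controls have still to receive whatever offer applies.

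**The case against.** The strongest reply is that the actual consent form and information sheet are not shown, and either could carry the Control Group terms. That limits the point: it concerns the consent discussion as section E describes it, and nothing can be said about what girls have in fact read. It does not remove the contradiction, because the inclusion criterion and section E are both operative text.

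It is also fair to say that controls are not simply short-changed. After a negative trial they are offered more than they were told. The direction depends on the result, as the table shows.

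A reader might infer more in three directions that the documents do not support.

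- **That control-arm retention will suffer by a calculable amount.** No text makes the offer the controls' main reason to return. The protocol also provides a graduation ceremony, six-monthly reunions, monthly peer groups, contraception and STI care, and about US$5 per data visit. A missed final visit need not remove a girl from the primary analysis either, since testing is six-monthly and the Poisson model accounts for duration of follow-up. Any figure for extra loss would be invented.
- **That one can state how often controls would get nothing under the entry wording.** If success meant a significant benefit on one two-sided 5% test, the chance would be 1 − 0.025 = 97.5% with no effect and 1 − 0.80 = 20% at the planned effect. If benefit on either of the two primary outcomes sufficed, and they were independent, it would be 0.975² ≈ 95% and 0.20² = 4%. Success is not defined, so neither pair can be relied on.
- **That the efficacy condition is unworkable because results come after the last visits.** The criterion and the consent section say only that receipt follows completion of the study, which allows time for analysis. The Control Group offer carries no efficacy condition. Each rule can be run on its own; they differ from each other.

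**Conclusion.** The point holds as an internal contradiction in the terms for controls. The inclusion criterion and the consent section agree with each other; the Control Group section differs from both in condition and in content, and nothing reconciles them. In three of the four situations a control can face, what she is told at entry differs from what the procedures provide.

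No estimand, analysis, sample size, power or error rate is affected. The weight of the point lies in the accuracy of what vulnerable participants agree to. A secondary, unquantified consideration is that stating any final-visit condition from the start may help control-arm follow-up. The conclusion rests on two readings: that the economic component at consent means the package defined in the Study Aims, and that the Control Group offer excludes those who miss the final visit. It should be corrected, and it can still be acted on for the 50 additional participants and for current controls.

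**What to change.** Make the inclusion criterion, section E and the Control Group section state one offer with the same condition and the same content. Carry it into the information sheet and consent form if they repeat section E. Do this before the 50 additional participants are consented, and give current controls the same statement at a scheduled visit.

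The sponsor and ethics bodies should confirm which offer governs:

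- **If the Control Group terms stand:** remove the success condition from the criterion and from section E. In both, say that training will be offered to all controls who complete the final visit. List what is covered (six months of fees) and what is not (transport, bonus, guidance counselling).
- **If the success condition stands:** define success, including what it means for the 50-participant feasibility cohort. Say when it will be known, and amend the Control Group section to match it in condition and content.

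The Control Group terms are already committed, so adopting them adds no expense beyond the wording. Either route needs an ethics amendment. Some controls will learn that the offer is smaller than described to them, and a mid-study notice may shift expectations in a behavioural trial. The notice should therefore be short, factual and the same for every control.

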**D. Subject Recruitment – Main Study**

**1. Sources:** In Zimbabwe, orphans and their families are eligible for funds collected through a countrywide AIDS tax paid by private citizens and businesses***.*** To distribute the funds, which are delivered on a monthly basis, each District AIDS Action Committee (DAAC)has developed and maintains a list of orphans, their ages and addresses through annual door-to-door and street-based enumeration. The DAAC under which Chitungwiza falls has agreed to assist us in recruiting orphans by referring them from their lists, while maintaining the confidentiality of the potential participants We will also be recruiting participants from community based venues such as market places and youth halls.

**2. Initial contact method:** During their monthly visits, DAAC members will describe the study to potential participants and invite those interested to contact us via visits to the clinics, email, telephone or project offices. When potential participants contact us, study staff will provide additional information about the study and will determine their eligibility. Participants recruited by study staff members will similarly be invited to visit the clinics and be screened for eligibility.

3. **Prevention for Positives cohort**: Approximately 40 participants screened for the main study were positive for HIV and/or HSV-2 and therefore not eligible. We will contact these 40 participants and invite them to re-screen for the study. If they are still eligible for the study for all other criteria, they will be invited to enroll. We will continue to recruit participants using procedures already described and approved (D, 1 and 2 above) until the desired sample size of 50 is reached. In this way stigma associated with being part of a new “positive” cohort will be avoided as the additional participants enrolled to meet our sample size will include both positive and negatives. No language or recruitment methods (flyers, outreach) will be employed that imply the new cohort is a “positive cohort’, nor single out any participant as positive throughout the process, and no changes will be made to recruitment documents. Additionally, the Chitunguiza CAB who is very supportive of Shaz, will be kept updated and involved from the beginning and will help manage any rumour or related misconceptions.

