**Aim 4:** **To evaluate whether characteristics related to participation, i.e., factors related to participant adherence, satisfaction, and understanding of the intervention mediate observed effects.** We will monitor participants’ adherence to the intervention (e.g., attendance at life skills and vocational trainings, required meetings), level of satisfaction with the program, and understanding of intervention content. We hypothesize that greater adherence, satisfaction, and level of understanding will be associated with positive biological and behavioral outcomes.

**Aim 5: To test the feasibility of expanding the intervention as designed to HIV and HSV-2 positive participants, and to test the feasibility of the intervention’s potential to support positive participants. (referred to as the *Prevention for Positives* component)** We hypothesize that with minor adjustments the intervention as designed will be adequate to meet the needs of positive clients in a fully integrative and confidential manner, with minimal fears of disclosure and without resultant discrimination or stigma. We hypothesize that the combined behavioral and economic intervention (intervention arm) will be more effective in empowering positive adolescents with improved economic livelihoods, better access to care and treatment, and slower disease progression, and will also effect behavior to prevent co-infection with other STI's and secondary transmission to partners, compared to the life skills intervention alone (control arm). We will monitor and record issues that arise through observation, in-depth interviews, supplemental questionnaires and trainer reports and to use these results to further refine the integrated social support facets of the intervention for future scale-up.

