**4. Methods**

**A. General Study Design**

We propose a randomized controlled trial of an intervention combining a vocational training package -- including a conditional stipend and completion bonus -- with life-skills education and social support, compared to life-skills education alone. The study will begin with six months of start-up activities, and enrollment will take place within a six-month period at the beginning of the study. The economic livelihood intervention and life-skills programs will be administered for one year and participants will be followed for one year post-intervention. Data collection and service provision to participants will be provided through a health clinic and occasional visits using a mobile clinic. The frequency of intervention visits (i.e. visits related to the intervention program such as life-skills training, SHAZ reunions, and vocational training) is described below. Visits for data collection, including biological and behavioral outcome data, will be collected at baseline, and every six months thereafter for a total of five visits over the three year period. We will follow participants for one year after the intervention to ensure sufficient power to examine our primary outcome (Aim 1) as well as to establish the temporal association between the intermediary effects of increased economic opportunity and improved sexual negotiation skills in enhancing participants’ control over sexual interactions (Aim 3). Finally one year of follow-up will allow us to assess the intervention’s sustained effects on high-risk behavior (Aim 2). (Please see appendices: Intervention Design and Study Design Flow Chart)

**Prevention for Positives component:** The SHAZ main study has completed its enrollment for the ongoing intervention study, with a total of n=315. In order to assess the feasibility of implementing this intervention with HIV and HSV-2 positive clients, we will enroll an additional cohort of n=50 according to the same criteria as was used in the main study, except that those who are HIV and/or HSV-2 positive also will be eligible to enroll.

In order to meet this objective, we will contact and invite all participants who screened out of the study because of positive results (n=40) and invite these to re-screen for the study. We will then continue to recruit additional participants until we meet the desired sample size n=50.

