- Utilize UZ-UCSF Programme referral protocols for positive study participants to facilitate access to national treatment services.
- Modify data collection tools to assess additional clinicial, behavioral, social and biological outcomes as appropriate.
- Incorporate ‘living positively’ tenants to all participants at Shaz reunions. Examples might include urban gardens and nutrition tips, etc.
- Adding qualitative interviews (and observations of Lifeskills sessions) among both control and interview participants (5 interviews each group, randomly selected, repeated over time) within the new cohort to assess issues such as group dynamics during, especially disclosure, stigma/discrimination and confidentiality.

Outcome measures to be added include:

- Clinical assessment of HIV related opportunistic infections including weight gain/loss
- CD4 counts to assess disease progression and need for referrals for treatment (CDV<250)
- Measures of disclosure, social support, experience of stigma or marginalization at home and in the community through supplemental questionnaires administrated during counseling sessions, qualitative interviews and observations of life skills sessions.

As the intervention and control trainings are designed for an initial group of 25 participants, a training session will begin each time that number of participants is achieved in a given arm. The intervention, which will be delivered in the first year of the study, will consist of five main components: 1) Life Skills education (UZ-UCSF) and basic home-based health care training (Red Cross) (intervention and control arm) 2) Guardian support 3) Choice of vocational training options as determined appropriate and available by SHAZ! guidance counselors (plus stipend/bonus, intervention only); 4) Guidance counseling for social support (intervention arm only) 5) Ongoing SHAZ reunions. There will be one year of follow-up during which time the reunions and study visits will be on-going every six months. (See intervention overview for details).

B. Overview of Intervention

i. Intervention Group

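### Prevention for Positives cohort: inviting all of the roughly 40 known positives before topping up to 50 does not secure the mixing said to prevent stigma, and limits what Aim 5 can conclude

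*Protocol*

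**What the plan says.** Aim 5 (Protocol, section 1, Study Aims) hypothesises that the intervention can serve positive girls "in a fully integrative and confidential manner, with minimal fears of disclosure and without resultant discrimination or stigma". It also hypothesises that the combined arm will do better than life skills alone among positive girls.

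The recruitment rule is in section 4.A (General Study Design) and section D, item 3:

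- "Approximately 40 participants screened for the main study were positive for HIV and/or HSV-2 and therefore not eligible". All of them are to be contacted and asked to re-screen.
- "If they are still eligible for the study for all other criteria, they will be invited to enroll".
- Ordinary recruitment then continues until 50 are enrolled. Neither a minimum of negatives nor a maximum of positives is stated.

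Section D, item 3 then says that stigma "will be avoided as the additional participants enrolled to meet our sample size will include both positive and negatives". It adds other protections: no wording or recruitment method that implies a positive cohort, no singling out of participants, unchanged recruitment documents, and involvement of the community advisory board.

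On eligibility, section C.3 states: "The only difference in inclusion/exclusion criteria for the additional 50 girls is that those who test positive" for HSV-2 or HIV are no longer excluded. Section 4.A reports that main-study enrolment is complete at 315 and that the 50 will be randomised as in the main study. Section F.1 sets training groups at 25, and "a training session will begin each time that number of participants is achieved in a given arm".

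**The concern.** The assurance in section D is worded as a certainty, and it rests on the mix of the cohort. The mix comes only from the places left after the recalled girls have enrolled, which may be as few as 10 of 50. The protocol neither controls that mix nor states what it expects.

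Two things are at stake. First, section G names loss of confidentiality as the primary risk and accepts that girls may be stigmatised if their status is learned. A safeguard against this should not be credited with more than the rule delivers. Second, Aim 5 is meant to inform integration and later scale-up. If the new groups are largely positive, what is learned about stigma, disclosure and group dynamics comes from a setting unlike one where a few positive girls join a mostly negative group.

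**Working it through.** The protocol gives no expected share of positives, so there is no figure to reproduce.

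**Inputs**

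- Known positives invited first: about 40 (sections 4.A and D).
- Cohort size: 50 (sections 4.A, C.3 and D).
- Training group size: 25, formed within an arm (section F.1). With 1:1 allocation, assumed from the main study's 150:150, 50/25 = 2 groups, or about one per arm.
- Uptake u, the fraction of the 40 who re-screen, remain eligible and enrol: not in the documents, so it is varied from 25% to 100%. Recalled girls are assumed still to test positive.
- Prevalence p of HIV and/or HSV-2 among the other recruits: the pilot findings (section 2.H) give HIV 9% and HSV-2 10% for orphans and out-of-school girls. The overlap is not given, so either infection lies between 10% (complete overlap) and 9% + 10% = 19% (none). p = 0 is added as a lower bound. As a rough cross-check, 40/(40 + 315) = 11.3%, which ignores girls screened out for other reasons.

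**Formula**

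Expected share positive = [40u + (50 − 40u)p] / 50 = p + 0.8u(1 − p).

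| Uptake u | Recalled girls enrolled | p = 0 | p = 10% | p = 19% |
|---|---|---|---|---|
| 25% | 10 | 10/50 = 20% | 14/50 = 28% | 17.6/50 = 35% |
| 50% | 20 | 20/50 = 40% | 23/50 = 46% | 25.7/50 = 51% |
| 75% | 30 | 30/50 = 60% | 32/50 = 64% | 33.8/50 = 68% |
| 100% | 40 | 40/50 = 80% | 41/50 = 82% | 41.9/50 = 84% |

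**Point at which positives reach half.** The recalled girls needed are (25 − 50p)/(1 − p). This is 25 at p = 0 (uptake 62.5%) and (25 − 9.5)/0.81 = 19.1 at p = 19% (uptake 48%).

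**Comparison with ordinary recruitment.** A group of 25 drawn from the same population with positives admitted would have 25 × 0.10 = 2.5 to 25 × 0.19 = 4.75 positives. At the same p, the new cohort exceeds this by 0.8u(1 − p), which is above zero at any uptake. At 25% uptake and p = 10% the cohort is 28% positive, or 7 of 25 against 2.5.

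**Balance between arms.** If 40 of the 50 are positive and the cohort is split 25/25 without stratification, the number of positives in one arm has mean 20 and SD √(25 × 0.8 × 0.2 × 25/49) = 1.43, with a 95% range of 17 to 23. A split of 23 to 17 in the arm comparison among positives is therefore within ordinary chance.

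**The case against.** The strongest reply is that the rule invites 40 girls and does not enrol 40. They must still be aged 16-19, out of school and not pregnant, and some will decline. Negatives are expected in every scenario: at full uptake, 50 − 41.9 = 8.1 to 50 − 40 = 10 of the 50. The protections listed in section D beyond the mix do not depend on it, and sections E, F and G add staff training on stigma, no disclosure to guardians without written consent, and restricted access to results. All of this stands.

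It also rules out four stronger readings that a reader might draw.

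- *That each new group will be about 80% positive.* That is the full-uptake figure, and the documents give no uptake.
- *That there is no protection against a recognisable positive cohort.* Some mixing and several other measures remain.
- *That Aim 5 cannot say anything about stigma.* Section F.1 measures disclosure, social support and stigma directly by questionnaire, interview and observation. The limit is on generalising the results.
- *That others can infer a girl's status from her being turned away and later accepted.* This is speculative. Pregnancy, age under 16 or being in school can also exclude a girl at first and resolve later, and nothing says that the referring committee learns screening results.

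What the reply does not answer is that the assurance is argued from the mix, while the rule leaves the mix uncontrolled and, at moderate to high uptake, mostly positive.

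**Conclusion.** The point holds as a mismatch between an unconditional assurance and a recruitment rule that does not secure it. The new groups could be about 40-51% positive at 50% uptake and 80-84% at full uptake, against about 10-19% under ordinary recruitment with positives admitted. These figures rest on assumed uptake, on p between 0 and 19%, and on roughly one new group per arm. The consequence for Aim 5 is limited but real: its stigma and disclosure results describe the composition actually delivered and may not carry over to groups where few girls are positive. The change should be made, but it does not invalidate the component.

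**What to change.** 1. In section D, item 3, replace the assurance that stigma will be avoided with a statement that mixing may reduce stigma but does not ensure its avoidance, and give the expected range of the mix. This belongs in the protocol text only, not in participant or recruitment materials.
2. Stratify randomisation of the 50 by serostatus, which is known at enrolment, so that the Aim 5 arm comparison among positives is balanced. The stratum should be handled only by staff whom section G already permits to see results.
3. Record the actual number of positives and negatives in each training group, and limit the Aim 5 stigma and scale-up conclusions to that composition.

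Two further steps may suggest themselves and are not recommended. A ceiling on re-invited girls would turn away willing participants from a component created to study them. Telling girls the expected share of positives would conflict with section D's own bar on wording that implies a positive cohort.

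The cost is a short amendment, minor extra allocation and reporting work, and care to keep the stratum confidential.
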